# Backgrounds

Out-of-hospital cardiac arrest (OHCA) is a critical medical emergency with substantial public health implications. The global incidence of OHCA ranges from 50 to 110 per 100,000 population annually [1]. Despite advances in resuscitation techniques, survival rates remain low, with less than 10% of patients surviving to hospital discharge [2]. The economic burden associated with OHCA is considerable, driven by both direct medical costs and indirect costs such as lost productivity, emphasizing the need for improved resuscitation strategies [3, 4].

In the prehospital setting, emergency medical technicians (EMTs) and paramedics are tasked with numerous responsibilities during resuscitation efforts [5]. These include checking vital signs, establishing intravenous or intraosseous access, administering medications and ensuring adequate chest compression and ventilation while transporting the patients. Effective ventilation is particularly challenging, often performed using a bag-valve-mask (BVM) device. Manual BVM ventilation can be inconsistent and labor-intensive, requiring one or more team members to focus solely on this task, which can detract from other critical resuscitation activities [6].

The American Heart Association (AHA) guidelines currently recommend manual BVM ventilation during cardiopulmonary resuscitation (CPR) [7]. However, this method is fraught with challenges, including the risk of hyperventilation, insufficient ventilation, and interruptions during chest compressions. These issues can compromise the quality of resuscitation and negatively impact patient outcomes.

Mechanical ventilation offers potential advantages over manual BVM ventilation. Studies have demonstrated that mechanical ventilators can provide more consistent and controlled ventilation [8]. For instance, Weiss et al. conducted a study comparing an automatic transport ventilator (ATV) with manual BVM ventilation. The results showed that the ATV allowed EMTs to accomplish additional tasks, improve documentation, and enhance overall patient care [9]. Similarly, the SYMEVECA phase 1 trial indicated that mechanical ventilators provided better ventilatory parameters compared to BVM, although the impact on clinical outcomes needs further investigation [8].

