## Exposure management

- - 1. Intervention group

The intervention group will receive APV for eligible patients, as determined by the selection criteria. The APV will be connected to the advanced airway (either SGA or ETT) in a standardized manner. The APV is set to deliver one breath every six seconds, with a tidal volume of 500-600 mL and a pressure limit of 60 mmHg. All other advanced cardiovascular life support (ACLS) procedures will follow the OHCA operation guidelines. If the APV malfunctions, the EMS team will switch to bag-valve-mask (BVM) ventilation.

- - 1. Control group

The control group will receive BVM ventilation for eligible patients, as determined by the selection criteria. The BVM will be connected to the advanced airway (either SGA or ETT) in the same manner as in the intervention group. The EMT will manually deliver a breath every six seconds.

- - 1. Advanced airway management

The decision to insert an SGA or perform ETT intubation depends on the level of the EMT attending the OHCA rescue. Only EMT-P personnel are authorized to perform ETT intubation. If an SGA is initially inserted, switching to ETT during the same dispatch is not permitted. If two attempts at ETT insertion fail, an SGA should be used instead.

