# Sample Size Estimation

In the original version of sample size calculation, we chose a secondary outcome (ventilation rate) to be the reference to calculate the sample size. Because we couldn’t find any studies with a similar trial design and primary outcome as our study. The original sample size was 260 patients. However, in August 2024, we identified some comparable studies to guide our calculations more precisely.

We chose the pilot study by Shin et al., which compared automatic mechanical ventilation (MV) with manual bag ventilation (BV) during CPR [19]. In that study, the primary outcome, any ROSC, was achieved in 56.7% of the MV group and 43.3% of the BV group—values closely aligning with our expected ROSC rates. Thus, we conducted an initial power analysis in G*Power 3.1 using the following parameters: Z test family, difference between two independent proportions, two-tailed test, proportions of 0.567 and 0.433, alpha of 0.05, power of 0.8, and equal allocation (1:1). This analysis suggested 218 patients per arm, totaling 436.

To account for the clustering effect due to randomization at the EMS team level, we included an intraclass correlation coefficient (ICC). Our EMS teams are expected to recruit 3 patients per cluster (over 14 days). Given the substantial variability in OHCA patient conditions, we assumed a low ICC of 0.06. The design effect was therefore calculated as 1+(3−1) ×0.06=1.12, adjusting our sample size to 488. Finally, with an estimated 5% dropout rate, the final required sample size was increased to 514 patients.

Figure 3. Sample size calculation by G*Power 3.1

[figure not shown]

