# Data Collection and Follow-up

Data will be collected in the REDCap database set up at National Taiwan University Hospital. The following variables will be gathered from the rescue reporting form: patient demographics (age and sex), pre-existing comorbidities (hypertension, diabetes mellitus, COPD, asthma, liver disease, kidney disease, heart disease, seizure, psychotic disorder, and cancer), arrest characteristics (witnessed arrest and bystander CPR), arrest location (household, workplace, public space, and nursing home), and EMT-performed procedures (oral/nasal airway, SGA, ETT, mechanical CPR, AED, defibrillation, IO/IV catheter, epinephrine injection, and normal saline infusion). Prehospital ROSC will also be reported on the form. These data will be collected on a weekly basis.

Other prognostic outcomes (any ROSC, 24-hour survival, survival to discharge, and neurological function at discharge) will be collected from the reports of the hospitals to which the patients are sent. Follow-up frequency for these outcomes will be one month.

Ventilation and chest compression feedback data will be exported from the Zoll X-series in .csv format. These files will be uploaded to the REDCap database on a weekly basis.

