# Analytic Plan

Statistical Package for the Social Sciences (version 26.0; IBM Corp., Armonk, NY, USA) will be used for the statistical analyses in this study. Intention to treat analysis will be adopted for comparing outcomes between interventions. Firstly, descriptive statistics of demographics (Table 1), ventilation parameters (Table 2), and outcomes (Table 3) among APV group and BVM group will be presented as number (percentage) for categorical variables and median (interquartile range) for continuous variables. Categorical variables will be compared using Pearson’s chi-square test or Fisher’s exact test, while continuous variables will be compared using Mann–Whitney U test. Secondly, multivariable logistic regression will be conducted to investigate the association of different ventilation interventions and patients’ outcomes, adjusting for potential confounders. Subgroup analysis, presented as a forest plot, will also be performed to investigate the impact of different interventions on outcomes in different subgroups. We will also compare the adjusted absolute difference between ventilation parameters measured in the APV and BVM group using the linear mixed-effects model (LMM). For the LMM, variables including demographics, prehospital information, resuscitation managements were included as fixed effects, whereas each patient will be modeled as a random effect. Two tail p-values <0.05 will be considered as statistically significant and will be corrected with Bonferroni correction in post-hoc analyses.

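### Both planned comparisons of ventilation rate look for a shift in centre and have little power if manual bagging errs about equally on both sides of the shared rate

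*Protocol*

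**What the plan says.** The Backgrounds section lists the difficulties of manual bag-valve-mask (BVM) ventilation, "including the risk of hyperventilation, insufficient ventilation, and interruptions during chest compressions". It also calls the manual method inconsistent and expects mechanical ventilation to be more consistent and controlled.

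Exposure management sets the automated pneumatic ventilator (APV) to one breath every six seconds and says of the control arm: "The EMT will manually deliver a breath every six seconds". Both arms therefore share a rate of 60/6 = 10 breaths/min. A tidal volume of 500-600 mL is stated as a device setting in the APV arm only.

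The first secondary objective is to compare ventilation parameters, and ventilation rate is a listed secondary outcome. For the analysis, the Analytic Plan states that "continuous variables will be compared using Mann–Whitney U test" and adds an adjusted absolute difference between arms from a linear mixed model with a patient random effect. Dummy Table 2 shows the median and interquartile range (IQR) by arm. The protocol specifies no deviation from target, no proportion in range and no comparison of spread.

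On data, Data Collection and Follow-up says: "Ventilation and chest compression feedback data will be exported from the Zoll X-series in .csv format".

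**The concern.** The argument for the device is about consistency: rates that are neither too fast nor too slow. The two comparisons fixed for rate ask something else, namely whether one arm's rates tend to be higher than the other's. If manual breaths are too fast in some patients and too slow in others, the centres of the two arms can agree while one arm is off target far more often. The formal result for rate under secondary objective 1 could then be non-significant in just the situation that the rationale describes.

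**Working it through.** **1. The plan's own figures.** The protocol gives no SD for ventilation rate, and the inputs behind its superseded 260 are not stated, so that number cannot be rebuilt. The current sample size can be. Inputs, from Sample Size Estimation: "two-tailed test, proportions of 0.567 and 0.433, alpha of 0.05, power of 0.8, and equal allocation (1:1").

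- n per arm = [1.960·√(2·0.5·0.5) + 0.842·√(0.567·0.433 + 0.433·0.567)]² / (0.567 − 0.433)² = (1.386 + 0.590)² / 0.01796 ≈ 217.4, so 218. The protocol agrees: "This analysis suggested 218 patients per arm, totaling 436".
- Design effect 1 + (3 − 1)·0.06 = 1.12, and 436 × 1.12 = 488.3, taken as 488.
- 488 / 0.95 = 513.7, so 514.

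The 218 per arm is used below.

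**2. What the two comparisons test.** Mann–Whitney is sensitive to departures of P(X<Y) + ½P(X=Y) from ½. If both arms are symmetric around the same centre, this quantity is exactly ½ whatever the two SDs are. The mixed model estimates a mean difference, which is then zero. Neither is built to detect a difference in spread around a shared target.

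**3. Size under balanced errors.** Assumptions: per-patient rate normal, both arms centred on 10/min, APV SD 1, BVM SD 2 to 5, illustrative band 8-12/min, clustering ignored, 2000 simulated trials per row. A t-test stands in for the mixed-model mean difference. The true share out of band is 2·[1 − Φ(2/SD)], which is 4.6% for APV.

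| BVM SD | BVM out of band | Mann–Whitney rejects | Mean difference rejects | Out-of-band proportions compared |
| --- | --- | --- | --- | --- |
| 2 | 31.7% | 5.6% | 5.0% | about 100% |
| 3 | 50.5% | 6.0% | 5.6% | about 100% |
| 4 | 61.7% | 7.6% | 5.0% | about 100% |
| 5 | 68.9% | 8.2% | 4.3% | about 100% |

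At 130 and 257 per arm the picture is the same: Mann–Whitney 5.4-8.8%, mean difference 4.3-5.8%. A separate run of 1000 trials at 244 per arm (488/2) gave Mann–Whitney rejection of 6.2% (SD 3) and 7.3% (SD 4). In that run, the same test applied to absolute deviation from 10/min rejected in 100%.

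**4. Sensitivity to balance.** With BVM SD 4 and 218 per arm, moving the BVM mean off 10/min gives:

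| BVM mean (per min) | Mann–Whitney power |
| --- | --- |
| 10 | 7.6% |
| 10.5 | 44% |
| 11 | 92% |
| 12 | about 100% |

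The blind spot is therefore narrow in the centre, though wide in the spread it can hide.

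**5. What dummy Table 2 would show.** For normal data the IQR is about 1.35·SD, so SDs of 1 and 4 give IQRs of about 1.3 and 5.4/min. The spread would be visible, but no estimate or test is attached to it, and an IQR does not count patients above or below a band.

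**The case against.** The strongest reply is that the plan answers the objective as worded. Over- and under-ventilation are background rationale. The hypothesis concerns ROSC, the secondary objective says only that ventilation parameters are compared, and no outcome is defined as consistency or time on target. This stands: the point is a mismatch between rationale and analysis, not a broken objective.

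Second, the low power needs nearly balanced errors, for which the protocol offers no evidence. The pilot randomised trial in out-of-hospital arrest tabulated in the Literature Review shows one-directional differences (tidal volume 267 against 507 mL, minute ventilation 3.1 against 6.7 L), which a location test can find. This also stands as a limit, although those figures concern volume and minute ventilation, not rate.

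Third, derived variables and bands often belong in an analysis plan, which is not shown here. That is true, but the protocol itself names both tests and lays out the table, and those choices do not fit its own argument.

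Two stronger readings are tempting. A reader might infer that the report would simply say there is no difference; the IQR in Table 2 argues against that. A reader might also infer that a significant shift could not show which arm was nearer the target. The printed medians can be set beside 10/min, so it could for the typical patient, though not for how often patients were off target.

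**Conclusion.** The point holds for ventilation rate, as a should-fix on a secondary outcome. If manual errors are roughly balanced around 10/min, with assumed SDs of 1 (APV) and 3-4 (BVM), the two planned comparisons reject in about 4-9% of trials. Meanwhile about 50-62% of BVM patients and 5% of APV patients lie outside the illustrative 8-12/min band. With a BVM mean of 11/min or more and SD 4, the planned test has at least about 92% power and the concern largely falls away as a matter of detection. The SDs, the normal shape, the band and the neglect of clustering are all assumptions.

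A reader might extend the point to every ventilation parameter. The protocol does not support that: only rate has a target shared by both arms, the stated volume is an APV setting, and end-tidal CO2 has no target. The primary ROSC analysis and the 514 are not touched.

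**What to change.** In the Analytic Plan, prespecify for ventilation rate:

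- a between-arm comparison of the absolute deviation from the protocol's own rate of one breath every six seconds, at patient level or at the finest resolution the Zoll export gives;
- the share of patients (or minutes) within, above and below a band that the sponsor fixes before analysis, with the shares above and below reported separately.

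Read these alongside the location tests for secondary objective 1, and keep the medians and IQRs. Confirm the resolution of the export first: the patient random effect suggests repeated measurements, but breath- or minute-level data are not stated. Extend the approach to tidal volume only if the sponsor states a volume target that applies to both arms. Do not apply it to end-tidal CO2.

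The cost is a few sentences, one derived variable, one additional secondary comparison and a band to fix in advance. At patient level it should need no new data, and it needs no extra patients at any level.

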## Outcome measurement

- - 1. Primary outcome

The primary outcome of the trial is any ROSC (defined as prehospital ROSC or ROSC achieved after in-hospital resuscitation).

- - 1. Secondary outcomes

The secondary outcomes include the following:

- Prehospital ROSC: ROSC before hospital arrival
- 24-hour survival
- Survival to discharge
- Neurological function on discharge
- Ventilation rate in prehospital resuscitation
- Tidal volume in prehospital resuscitation
- End-tidal CO2 level in prehospital resuscitation
- Chest compression fraction in prehospital resuscitation
- Intravenous catheter insertion in prehospital resuscitation
- Epinephrine injection in prehospital resuscitation
- Satisfaction of EMT in prehospital resuscitation (Appendix 2)

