## Interim analysis and stopping criteria

- - 1. All ROSC (Return of Spontaneous Circulation) Events

If the number of ROSC events in one group significantly exceeds that of the other group, as determined by a chi-square test in a 2x2 table, and if this difference reaches statistical significance (p-value < 0.05), the study may be terminated.

- - 1. Adverse Events

The known potential adverse event related to the ventilator that could be assessed in this study is barotrauma (pressure-related injury to the airway). However, considering that the study subjects are OHCA (out-of-hospital cardiac arrest) patients, and not all of them can be evaluated for the occurrence of barotrauma under standard medical practice, the threshold for adverse events in this study is set at 5%. If more than 15 cases of potential barotrauma (e.g., pneumothorax) occur in the experimental group, the study must be terminated.

- - 1. Other criteria
       1. Changes in government emergency medical services policies
       2. The APV is found to be harmful to humans during the study
       3. Major compromise to the EMS work due to the study

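### The Analytic Plan tests the primary outcome twice at two-sided 0.05, unadjusted and adjusted, without saying which test decides, and neither test as written allows for the randomised clusters

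*Protocol*

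**What the plan says.** Protocol, Outcome measurement, fixes the endpoint: "The primary outcome of the trial is any ROSC (defined as prehospital ROSC or ROSC achieved after in-hospital resuscitation").

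Protocol, Analytic Plan, analyses it in two steps.
- The first step is tabulation with group comparison: "and outcomes (Table 3) among APV group and BVM group will be presented as number (percentage) for categorical variables", followed by "Categorical variables will be compared using Pearson’s chi-square test or Fisher’s exact test". Any ROSC is a row of dummy Table 3, so this test covers the primary outcome.
- The second step is the regression: "multivariable logistic regression will be conducted to investigate the association of different ventilation interventions and patients’ outcomes, adjusting for potential confounders". Patients' outcomes again include any ROSC.

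One significance rule closes the section: "Two tail p-values <0.05 will be considered as statistically significant and will be corrected with Bonferroni correction in post-hoc analyses". Neither step is called primary, main or confirmatory.

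Two other sections use an unadjusted test of the same endpoint. Sample Size Estimation uses "Z test family, difference between two independent proportions, two-tailed test". Interim analysis and stopping criteria judges the ROSC difference "as determined by a chi-square test in a 2x2 table".

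**The concern.** The hypothesis concerns one binary outcome, and the plan gives two p-values for it, each held to 0.05. If they fall on opposite sides of the threshold, the protocol does not say which one answers the hypothesis. Both answers can be defended afterwards. The sizing and interim tests favour the unadjusted result. The Analytic Plan, however, opens its first step as descriptive and assigns the question of association with outcomes to the regression. In an open-label trial, that choice should be fixed before the outcomes are known.

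Two things are at stake: a type I error somewhat above 5% if either test may establish success, and a borderline conclusion that depends on which test is quoted.

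Choosing one of the two tests as written would not by itself secure the 5% level. The trial randomises two-week clusters and is sized for that, but a patient-level chi-square test ignores the clusters and the logistic model is given no cluster term. The only random effect in the section is for the patient, in the mixed model for ventilation parameters.

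**Working it through.** **1. The plan's own sample size (Sample Size Estimation).** Inputs: "Z test family, difference between two independent proportions, two-tailed test, proportions of 0.567 and 0.433, alpha of 0.05, power of 0.8", equal allocation, intraclass correlation 0.06, 3 patients per cluster, 5% dropout.

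n per arm = [1.96·√(2·0.5·0.5) + 0.8416·√(0.567·0.433 + 0.433·0.567)]² / (0.567 − 0.433)²
= [1.3859 + 0.5898]² / 0.017956 = 217.4, so 218 per arm and 436 in total.

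Design effect = 1 + (3 − 1)·0.06 = 1.12. 436·1.12 = 488.3, taken as 488. 488/0.95 = 513.7, so 514.

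The stated figures reproduce. The sizing therefore rests on an unadjusted two-proportion test at two-sided 0.05, inflated for clustering.

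**2. Two tests, either sufficient, under the null.** With z₁ (unadjusted) and z₂ (adjusted) bivariate normal with correlation ρ, the chance of at least one significant result is 1 − P(|z₁| < 1.96 and |z₂| < 1.96). The documents do not give ρ, so a range is shown.

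| Assumed ρ | P(at least one p < 0.05) |
|---|---|
| 0.95 | 0.0646 |
| 0.90 | 0.0704 |
| 0.80 | 0.0781 |
| 0.70 | 0.0835 |
| 0 (independent tests) | 1 − 0.95² = 0.0975 |

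**3. Patient-level simulation.** This used 488 patients, 1:1, one adjusted model with four fixed normal covariates, and no clustering. The joint standard deviation of the covariates on the logit scale is assumed. There were 10,000 null trials and 4,000 trials at 56.7% vs 43.3% per setting.

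| Covariate SD (logit) | Either test significant, null | Tests disagree, null | Tests disagree, planned effect | Correlation of the two statistics, null |
|---|---|---|---|---|
| 0.5 | 6.6% | 2.5% | 5.1% | 0.97 |
| 1.0 | 6.8% | 3.9% | 8.5% | 0.91 |
| 1.5 | 7.9% | 5.4% | 11.2% | 0.84 |
| 2.0 | 8.1% | 6.1% | 13.0% | 0.77 |

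Each test alone stays near 5% under the null (4.8% to 5.5%). The excess comes from allowing either to count.

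**4. Ignoring the clusters.** If the true variance of the treatment contrast is 1.12 times what a patient-level test assumes, its real two-sided error is 2·[1 − Φ(1.96/√1.12)] = 2·[1 − Φ(1.852)] ≈ 0.064. This uses only the protocol's own design effect. It is a separate source of error from step 2. The two were not combined, and the percentages should not simply be added.

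**The case against.** The best defence is that the protocol already leans one way. The sizing and interim tests are unadjusted, the chi-square comparison comes first, dummy Table 3 shows crude counts and percentages with no adjusted odds ratio, and the regression is introduced in exploratory language. On this reading the unadjusted test is primary and the model supportive, and the sections do not contradict one another. That lean is real. But no section says that the unadjusted test decides the final result, and both tests share one threshold.

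A second defence is that covariate lists are usually left to a statistical analysis plan, which may exist unseen. This stands: the missing list is not in itself a fault here. The point rests on what the protocol does state, namely two tests of its primary outcome at the same level with no order between them.

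A reader might go further and infer that the open phrase about confounders lets the sponsor search many covariate sets, so that the error rate climbs well beyond 8%. The documents do not support that. Nothing in them provides for choosing a model by its result, and the list may be fixed elsewhere. Nor is 9.75% a fair figure for this trial. It assumes independent tests, whereas two analyses of the same outcome in the same patients are strongly correlated.

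**Conclusion.** The point holds, at modest size. If either analysis may establish success, the type I error is about 6.5%-8% rather than 5%, for one fixed adjusted model and a correlation of 0.95-0.80 between the tests. At the planned effect the two analyses agree in most trials and disagree in roughly 5%-13%. The correlation and covariate strengths behind these figures are assumptions, and the simulation leaves out clustering and the interim look.

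The clustering part rests on the protocol's own design effect: about 6.4% for a single naive test. It means that naming one of the two tests exactly as written would remove the ambiguity but not fully restore the 5% level.

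The documents do not show that the sponsor intends to choose the more favourable result, or that the two tests usually conflict. The protocol leaves open a choice that it can close cheaply.

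**What to change.** In the Analytic Plan, name one deciding analysis of any ROSC. The preferred form is a logistic model with treatment and a fixed set of covariates already collected under Data Collection and Follow-up that the allocated device cannot affect: age, sex, witnessed arrest, bystander CPR and arrest location. Procedures that the EMTs perform under the allocated arm should stay out, although dummy Table 1 lists them as baseline; intravenous access and epinephrine are also secondary outcomes. Standard errors should respect the randomised cluster-periods, and the result should be reported as a marginal risk difference with its 95% confidence interval. State that the other comparison is supportive only and cannot establish success.

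An unadjusted primary comparison that respects the clusters would resolve the point equally well and would match the test used for sizing.

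The cost is one or two sentences and no new data. The sponsor gives up the option of quoting the more favourable analysis. If the adjusted model is chosen, the primary analysis will differ from the sizing test, which the protocol should acknowledge.

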Despite these advantages, most research on mechanical ventilation during CPR has focused on in-hospital settings. The use of automated pneumatic ventilators (APVs) in the prehospital environment remains underexplored. APVs are designed to deliver consistent ventilation with minimal manual intervention, potentially freeing up EMTs to perform other critical tasks during resuscitation. This could be particularly beneficial in prehospital settings where resources and personnel are often limited [9].

There is a significant knowledge gap regarding the effectiveness of APVs as a substitute for BVMs in prehospital OHCA management. Key concerns include whether APVs can deliver sufficient ventilation without causing high plateau pressures that may lead to barotrauma. Addressing this gap is crucial for developing evidence-based guidelines that can enhance prehospital care and improve patient outcomes. This study aims to evaluate the effectiveness of APVs compared to traditional BVMs in the prehospital resuscitation of OHCA patients.

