# Dummy Tables

| Table 1. Baseline characteristics | | |
| --- | --- | --- |
|  | APV | BVM |
|  | (n=XXX) | (n=XXX) |
| Age, years (mean ± SD) | XX ± XX | XX ± XX |
| Males, n (%) | XX (XX.X%) | XX (XX.X%) |
| Pre-existing comorbidity |  |  |
| Diabetic mellitus, n (%) | XX (XX.X%) | XX (XX.X%) |
| Hypertension, n (%) | XX (XX.X%) | XX (XX.X%) |
| Cancer, n (%) | XX (XX.X%) | XX (XX.X%) |
| COPD, n (%) | XX (XX.X%) | XX (XX.X%) |
| Asthma, n (%) | XX (XX.X%) | XX (XX.X%) |
| Stroke, n (%) | XX (XX.X%) | XX (XX.X%) |
| Liver disease, n (%) | XX (XX.X%) | XX (XX.X%) |
| Kidney disease, n (%) | XX (XX.X%) | XX (XX.X%) |
| Heart disease, n (%) | XX (XX.X%) | XX (XX.X%) |
| Seizure, n (%) | XX (XX.X%) | XX (XX.X%) |
| Psychotic disorder, n (%) | XX (XX.X%) | XX (XX.X%) |
| Witnessed arrest, n (%) | XX (XX.X%) | XX (XX.X%) |
| Bystander CPR, n (%) | XX (XX.X%) | XX (XX.X%) |
| Arrest location |  |  |
| Household, n (%) | XX (XX.X%) | XX (XX.X%) |
| Working place, n (%) | XX (XX.X%) | XX (XX.X%) |
| Public space, n (%) | XX (XX.X%) | XX (XX.X%) |
| Nursing home, n (%) | XX (XX.X%) | XX (XX.X%) |
| Others, n (%) | XX (XX.X%) | XX (XX.X%) |
| Oral airway, n (%) | XX (XX.X%) | XX (XX.X%) |
| Nasal airway, n (%) | XX (XX.X%) | XX (XX.X%) |
| SGA, n (%) | XX (XX.X%) | XX (XX.X%) |
| ETT, n (%) | XX (XX.X%) | XX (XX.X%) |
| Mechanical CPR, n (%) | XX (XX.X%) | XX (XX.X%) |
| AED, n (%) | XX (XX.X%) | XX (XX.X%) |
| Defibrillation, n (%) | XX (XX.X%) | XX (XX.X%) |
| IO, n (%) | XX (XX.X%) | XX (XX.X%) |
| IV, n (%) | XX (XX.X%) | XX (XX.X%) |
| Epinephrine, n (%) | XX (XX.X%) | XX (XX.X%) |
| Normal saline, n (%) | XX (XX.X%) | XX (XX.X%) |

| Table 2. Ventilation parameters between patients in APV and BVM group | | |
| --- | --- | --- |
|  | APV | BVM |
|  | (n=XXX) | (n=XXX) |
| Ventilation rate, bpm (median ± IQR) | XX ± XX | XX ± XX |
| Tidal volume, mL (median ± IQR) | XX ± XX | XX ± XX |
| EtCO2, mmHg (median ± IQR) | XX ± XX | XX ± XX |

| Table 3. Outcome comparison between patients in APV and BVM group | | |
| --- | --- | --- |
|  | APV | BVM |
|  | (n=XXX) | (n=XXX) |
| Prehospital ROSC, n (%) | XX (XX.X%) | XX (XX.X%) |
| Any ROSC, n (%) | XX (XX.X%) | XX (XX.X%) |
| 24-hour survival, n (%) | XX (XX.X%) | XX (XX.X%) |
| Survival to hospital discharge, n (%) | XX (XX.X%) | XX (XX.X%) |
| Good neurological function after discharge, n (%) | XX (XX.X%) | XX (XX.X%) |

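### The mixed model for ventilation parameters adjusts for resuscitation management given after allocation, and two secondary outcomes (IV insertion and epinephrine) are tabulated as baseline characteristics

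*Protocol*

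**What the plan says.** The Analytic Plan contains three layers of comparison.

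- **Unadjusted tests.** "Categorical variables will be compared using Pearson’s chi-square test or Fisher’s exact test", with Mann–Whitney tests for continuous variables. Intention to treat is adopted.
- **Logistic regression for patient outcomes.** "multivariable logistic regression will be conducted to investigate the association of different ventilation interventions and patients’ outcomes, adjusting for potential confounders". The confounders are not listed.
- **Linear mixed model for ventilation parameters.** The plan will "compare the adjusted absolute difference between ventilation parameters measured in the APV and BVM group using the linear mixed-effects model (LMM"). For this model, "variables including demographics, prehospital information, resuscitation managements were included as fixed effects", with patient as a random effect. Dummy Table 2 shows the parameters: ventilation rate, tidal volume and EtCO2.

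Outcome measurement lists among the secondary outcomes "Intravenous catheter insertion in prehospital resuscitation" and "Epinephrine injection in prehospital resuscitation". In the Dummy Tables, IO, IV, epinephrine, saline, airway devices, mechanical CPR and defibrillation are all rows of "Table 1. Baseline characteristics". Table 3, the outcome table, has no row for IV or epinephrine.

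The Backgrounds section describes the device as "potentially freeing up EMTs to perform other critical tasks during resuscitation".

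**The concern.** A covariate in a randomised comparison should be something the allocated arm cannot alter. Resuscitation management does not meet that condition. Crews know the arm before the patient's arrest, and the rationale for the device is partly that it changes how crews spend their time.

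If the device does change a procedure, holding that procedure constant causes one of two problems. Where the procedure affects the outcome, adjustment strips out part of the device effect. Where procedure and outcome share an unmeasured cause, such as severity or duration of the arrest, adjustment introduces a difference that is not due to the device. Either way, the adjusted figure is no longer the total effect of assignment that an intention-to-treat analysis targets.

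There is also an inconsistency that needs no causal argument: two declared outcomes are laid out as baseline variables.

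**Working it through.** **Step 1. Is the management delivered after allocation?** Randomization and blinding sets 14-day periods and says EMTs and hospital staff cannot be blinded. Study procedures and workflow has the allocation announced on Friday evening for a Monday 8 AM start. The arm is therefore known before any patient in that period is treated, and every crew procedure follows it.

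**Step 2. Does the protocol expect the device to alter management?** Yes. The Backgrounds rationale says so, the literature review cites a randomised trial in which crews accomplished more tasks with an automatic ventilator, and resuscitation quality is a secondary objective.

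**Step 3. What are the management variables?** The Analytic Plan does not itemise them. The only list of crew procedures is in Data Collection and Follow-up: oral or nasal airway, SGA, ETT, mechanical CPR, AED, defibrillation, IO/IV catheter, epinephrine and normal saline. That IV and epinephrine would be among the covariates is a reasonable inference from this list and from Table 1; it is not stated.

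**Step 4. Which model is affected?** The clause belongs to the mixed model for ventilation parameters only.

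**Step 5. What can adjustment do?** The protocol gives no figure to reproduce on this point, so the following is an illustration and every input is assumed. With T the arm, U an unmeasured standard normal prognostic factor, and M a binary procedure:

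- logit P(M = 1) = bT + gU
- Y = 30 + 2T + mM + 5U + error (SD 8)

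There are 400,000 simulated patients and one value of Y per patient in arbitrary units. The arm coefficient is estimated by ordinary least squares with and without M, which simplifies the planned mixed model.

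| b | g | m | M given, BVM / APV | Without M | With M |
| --- | --- | --- | --- | --- | --- |
| 0 | 0 or −1 | 0 or 3 | 50% / 50% | 2.03 | 2.03 |
| 1.0 | 0 | 0 | 50% / 73% | 2.03 | 2.03 |
| 0.5 | 0 | 3 | 50% / 62% | 2.40 | 2.03 |
| 1.0 | 0 | 3 | 50% / 73% | 2.72 | 2.03 |
| 0.5 | −1 | 0 | 50% / 60% | 2.03 | 2.46 |
| 1.0 | −1 | 0 | 50% / 70% | 2.03 | 2.85 |
| 0.5 | −1 | 3 | 50% / 60% | 2.34 | 2.46 |
| 1.0 | −1 | 3 | 50% / 70% | 2.62 | 2.85 |

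Hand check of the fourth row: the total effect is 2 + 3 × (0.73 − 0.50) = 2.69, against 2.72 simulated. The standard error of the simulated difference is about 2 × √(25 + 64) / √400,000 = 0.03, which also explains 2.03 in place of 2.

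Adjustment lowers the estimate when M is purely a mediator (2.72 − 2.03 = 0.69), raises it when M only shares a cause with the outcome (2.85 − 2.03 = 0.82), and does nothing when the arm does not change M or when M is unrelated to the outcome.

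**The case against.** The strongest reply is about reach. The clause governs one secondary analysis. A reader might infer that any ROSC, the primary outcome, will be adjusted for IV access and epinephrine. The documents do not say this: the logistic model's confounders are unlisted, nothing says Table 1 is their source, and an itemised list may properly sit in an analysis plan that is not shown. Read strictly, a variable that follows randomised allocation is not a confounder at all. This stands. All that can be said of the logistic model is that its wording does not rule such variables out, while the same paragraph accepts them in the mixed model.

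Second, the task-freeing argument fits ROSC better than ventilation parameters. Under Exposure management, APV fixes the rate at one breath every six seconds and the tidal volume at 500–600 mL, so its effect on those two runs mainly through the settings. This also stands in part: mediation through IV access or epinephrine is not an evident route for rate or tidal volume. EtCO2, a measured patient response, is the more arguable case. The shared-cause route does not need mediation.

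Third, airway type depends on crew level and the scene, is settled before the device is connected, and could usefully explain variation in tidal volume. That makes a device effect on airway choice less likely, but the choice is still made with the arm known, so it is not a safe default covariate.

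Fourth, unadjusted comparisons are planned and do not depend on the covariate choice. That is correct and limits the damage.

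**Conclusion.** The point holds for the mixed model and for the dummy tables. The protocol commits the adjusted comparison of ventilation rate, tidal volume and EtCO2 to undefined management variables that follow an unblinded allocation, and it shows two secondary outcomes only as baseline characteristics.

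The bias is conditional. It arises only if the device changes a procedure included in the model and that procedure affects the outcome or shares an unmeasured cause with it. It can go either way, and the protocol gives nothing from which to size it; the simulated values show direction, not magnitude. No figure is offered for ROSC, because the model for ROSC is not stated to include these variables.

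Two stronger conclusions are not supported: that adjustment will necessarily remove the device effect, and that the trial's main question goes unanswered. On this point the unadjusted intention-to-treat comparisons remain intact.

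**What to change.** 1. In the Analytic Plan, delete resuscitation management from the mixed model's fixed effects. Replace the general categories with a named list of covariates settled before the arm can act and already collected: age, sex, comorbidity, witnessed arrest, bystander CPR and arrest location.
2. Apply the same limit to the logistic model's confounders, in the protocol or the SAP.
3. Move the crew-performed procedures (airway devices, mechanical CPR, AED, defibrillation, IO, IV, epinephrine, saline) out of Table 1 into a table of care after allocation. Report IV insertion and epinephrine there or in Table 3 as secondary outcomes.

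The cost is a wording change and revised table shells. No new data are needed, and the sample size of 514 is unchanged because its calculation uses no covariates.
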